# A single-blinded, single-centre, controlled study in healthy adult smokers to identify the effects of a reduced toxicant prototype cigarette on biomarkers of exposure and of biological effect versus commercial cigarettes

**DOI:** 10.1186/1471-2458-13-690

**Published:** 2013-07-29

**Keywords:** Biomarker of exposure, Biomarker of biological effect, Tobacco smoke toxicants, Reduced toxicant prototype cigarettes, Potential reduced-exposure product, PREP, Modified risk tobacco product, MRTP, Smoking

## Abstract

**Background:**

Despite universal acceptance that smoking is harmful, a substantial number of adults continue to smoke. The development of potential reduced exposure products (more recently termed modified risk tobacco products) has been suggested as a way to reduce the risks of tobacco smoking. This trial is designed to investigate whether changes in toxicant exposure after switching from a commercial to reduced toxicant prototype (RTP) cigarette (7 mg International Organisation for Standardisation (ISO) tar yield) can be assessed by measurement of biomarkers and other factors. The primary objective is to descriptively assess changes in selected biomarkers of exposure (BoE) and biomarkers of biological effect (BoBE) within participants and within and between groups after switching. Secondary objectives are to assess similarly changes in other biomarkers, quality of life, smoking behaviours, physiological measures, mouth-level exposure to toxicants and sensory perception.

**Methods/design:**

This trial will assess current smokers, ex-smokers and never-smokers in a single-centre single-blind, controlled clinical trial with a forced-switching design and in-clinic (residential) and ambulatory (non-residential) periods. Smokers will be aged 23–55 years (minimum legal smoking age plus 5 years) and non-smokers 28–55 years (minimum legal smoking age plus 5 years, plus minimum 5 years since last smoked). Smokers will be allowed to smoke freely at all times. We will assess changes in selected BoE and BoBE and effective dose in urine and blood after switching. Creatinine concentrations in serum, creatinine clearance in urine, cotinine concentration in saliva, diaries and collection of spent cigarette filters will be used to assess compliance with the study protocol. Mouth-level exposure to toxins will be assessed by filter analysis.

**Discussion:**

Data from this study are expected to improve scientific understanding of the effects of RTP cigarettes on BoE and BoBE, and give insights into study design for clinical assessment of potential MRTPs.

**Trial registration:**

The study was registered in the Current Controlled Trials database under the reference ISRCTN81286286.

## Background

Despite universal acceptance that smoking is harmful, a substantial number of adults continue to smoke. There is likely to continue to be a substantial population of smokers for the foreseeable future (1.6 billion smokers worldwide is predicted in the year 2040) even with the current tobacco control measures [1]. The concept of tobacco harm reduction, defined by the US Institute of Medicine (IOM) as “decreasing total morbidity and mortality, without completely eliminating tobacco and nicotine use” [2] is being considered by some regulators.

### Development of potential reduced-exposure products

In the 2001 IOM report, *Clearing the Smoke: the scientific basis for tobacco harm reduction*[2], the development of potential reduced-exposure products (PREPs) was suggested as a possible way to achieve tobacco harm reduction. A PREP was defined as a product that results in substantial reduction in exposure to one or more tobacco toxicants and that can reasonably be expected to reduce the risk of developing one or more specific diseases or other adverse health effects. The types of studies, including clinical trials, required to assess PREPs are being considered [3]. In 2011 the IOM issued a further report on the science needed to assess modified risk tobacco products (MRTPs) in response to the US FDA who have released draft guidance on this.

In addition, a scientific committee that advises the World Health Organization (WHO) has recommended the mandated reduction of certain cigarette smoke toxicants [4]. The potential for toxicant exposure and risk reduction may be tested by the development and assessment of reduced toxicant prototype (RTP) cigarettes. An RTP has been developed with the use of novel technologies related to tobacco, filter, and cigarette format which have been employed to reduce the yields of smoke toxicants. The tobacco used in the RTP has been selected for smoking acceptability and chemistry profiles (e.g., low in tobacco-specific nitrosamines and heavy metals) and a proportion of the blend prepared with a new process where tobacco is extracted with water and the extract and fibres are treated separately to reduce certain toxicant precursors before being recombined [5]. Additionally, an inert non-tobacco sheet that contains a high percentage of glycerol is also cut and mixed with the tobacco to dilute the concentrations of smoke toxicants during smoking [6]. In order to reduce the yields of some vapour phase toxicants, filters in the RTP incorporated a highly adsorbent form of carbon [7] and a selective amine-functionalised resin [8].

### Previous clinical study assessments

The tools to assess exposure to smoke toxicants were examined in two previous clinical studies conducted in Germany and Canada using conventional cigarettes. These studies aimed to assess whether the available techniques could adequately assess human smoke exposure by filter analysis and measurement of biomarkers of exposure (BoE) [9-11]. These enable the exposure tobacco smoke toxicants or their metabolites to be measured in urine, or other biologic matrices. Both studies showed a good correlation between exposure estimates from the two methods, and, in the case of the German study, the methods were senstive enough to detect changes in smoke exposure following a switch to a cigarette with a lower International Organization for Standardization (ISO) tar yield [10].

Technologies used in the RTPs have previously been shown to significantly reduce yields of a range of tobacco smoke toxicants by 10% to 95% compared with typical commercial products with equivalent ISO tar yields [12]. A clinical study of these RTPs, using a short-term (6-week) switching design, determined smoke toxicant exposure by measurement of various BoE in current smokers after they switched from conventional cigarettes to an RTP (ISRCTN 72157335) [13]. This study showed that toxicant exposure was reduced after switching to the RTP, although the prototypes required further development to optimise the reductions and improve acceptability to smokers.

However, reductions in smoke toxicant exposure alone should not be assumed to result in a reduction in smoking-related risk, and the studies noted above did not investigate the potential for a reduction in risk of smoking-related diseases or adverse biological effects. Biomarkers of biological effect (BoBE) may serve as biological indicators of the body’s response to smoke exposure. These include modifications in some parameters of blood composition, alterations in activity of specific enzymes, the appearance of DNA adducts, localised increases in messenger RNA and protein concentrations, and the appearance of specific antibodies (autoantibodies). BoBE may differ between smokers, non-smokers and ex-smokers [3,14]. Ideally, smoking-related biomarkers should be detectable early and have plausible links to the early stages of smoking-related diseases. While reductions in exposure to toxicants can be seen within 2–4 weeks by measurement of BoE, it is anticipated that changes in biological effect measurable by changes in BoBE, physiological or quality-of-life assessments would take longer to manifest. Hatsukami *et al.*[3] recommended that a series of clinical studies of both short and intermediate duration be performed in the assessment of PREPs/MRTPs. Previous studies (unpublished data) indicate that a period of 6 months should be sufficient to demonstrate the effects of reductions in exposure.

Three biomarkers have been identified that are suggested in the literature to have the potential to enable assessment of participant compliance [15,16]. These biomarkers, termed biomarkers of effective dose (BoED), are DNA and protein adducts of identified smoke toxicants that have relatively long half-lives (50–55 days). Interrogation of these data, therefore, could be useful for the monitoring of behaviour and compliance over extended periods of time.

Other elements to consider in clinical studies are mouth-level exposure (MLE) to tar and nicotine [13] and whether changes in exposure affect any basic physiological features or quality of life. Sensory features are also important to assess, particularly in relation to compliance to protocol in a switching study.

### Study hypothesis and objectives

The study is intended to test the hypothesis that switching of smokers from conventional cigarettes to RTP cigarettes will result in measurable reductions in exposure to toxicant and lead to beneficial changes in biological effects, as shown by assessment of biomarkers.

The primary objective of this study is to descriptively assess changes in selected BoE and BoBE (Table 1), within participants and within and between groups, after a forced switch from a commercial control cigarette to an RTP cigarette of equivalent ISO tar yield. Secondary objectives are to descriptively assess changes within participants and within and between groups in further BoE, BoBE and BoED, quality of life, smoking behaviours, physiological measures, MLE and sensory perception, and to descriptively assess changes in the primary and secondary end points together after switching, in comparison with values for ex-smokers and never-smokers (Table 1). Data from this study are expected to improve the scientific understanding of tobacco products.

**Table 1 T1:** Parameters in primary and secondary endpoints

**Primary endpoints**	
***Biomarkers of exposure***	
	• Urine: Nicotine, cotinine, 3-hydroxycotinine and their glucuronide conjugates, acrolein metabolite (3-HPMA), crotonaldehyde metabolite (HMPMA), TSNA metabolites (total NNAL, total NNN, total NAT, total NAB), 1,3-butadiene metabolite (MHBMA), acrylonitrile metabolite (CEMA) and aromatic amines (4-aminobiphenyl, 3-aminobiphenyl, o-toluidine, 2-aminonaphthalene), plus 9 PAH metabolites (1-Hydroxynapthalene, 2-Hydroxynapthalene, 2-Hydroxyflourene, 1-, 2-, 3-, 4, and 9-Hydroxyphenanthrene, 1-Hydroxypyrene)
	• Salivary cotinine
	• Exhaled CO
***Biomarkers of biological effect:***	
	• Urine: F_2_-isoprostane (8-iso-PGF2 Type III and VI; for oxidative stress)
	• Blood: white blood cells (for cardiovascular disease)
	• Plasma: sICAM-1 (for cardiovascular disease)
**Secondary endpoints**	
***Biomarkers of exposure***	
	• Urine: urine mutagenicity (Ames test)
***Biomarkers of biological effect***	
	• Urine: 8-OHdG, cis-thymidine glycol, 11-dehydrothromboxane B2
	• Blood: gene expression, neutrophil count, monocyte count
	• Erythrocytes: haemoglobin, superoxide dismutase activity, glutathione peroxidase, glutathione reductase, catalase activity, malondialdehyde
	• Plasma or serum: IL-6, IL-8, ascorbic Acid, dehydroascorbic Acid, total antioxidant capacity, hsCRP (males), fasting (12 h) lipid profile (total cholesterol, LDL, HDL, Triglycerides), fibrinogen, MCP-1, neutrophil elastase, MMP-1, MMP-9, TIMP-1, LTB4, TNF-α, VEGF, oxLDL
***Other features***	
	• Filter analysis: MLE to nicotine and ‘tar’ (nicotine-free dry particulate matter [NFDPM])
	• Sensory testing questionnaire
	• QoL questionnaire
	• Smoking behaviours questionnaire
	• Puffing and inhalation behaviour
	• Pulmonary function test (FEV, FEV1, PEF)
	• Biomarkers of Effective Dose (compliance monitoring)
	• Haemoglobin adducts in blood: Acrylonitrile (2-Cyanoethylvaline) and 4-ABP

*3-HPMA*, 3-Hydroxypropylmercapturic acid; *HMPMA*, 3-hydroxy-1-methylpropylmercapturic acid; *TSNA*, Tobacco-specific nitrosamine; *NNAL*, 4-(methylnitrosamino)-1-(2-pyridyl)-1-butanol; *NNN*, *N*-nitrosonornicotine; *NAT*, *N*-nitrosoanatabine; *NAB*, *N*-nitrosoanabasine; *MHBMA*, monohydroxybutenylmercapturic acid; *CEMA*, 2-cyanoethylmercapturic acid; *PAH*, Polyaromatic hydrocarbons; *CO*, Carbon monoxide; *PGF2*, prostaglandin F2; *sICAM-1*, soluble intercellular adhesion molecule; *8-OHdG*, 8-oxo-2′-deoxyguanosine; *IL-6*, Interleukin 6; *IL-8*, Interleukin 8; *hsCRO*, high-sensitivity C-reactive protein; *LDL*, Low-density lipoprotein; *HDL*, High-density lipoprotein; *MCP-1*, Monocyte chemotactic protein-1; *MMP-1*, Matrix metalloproteinase-1; *MMP-9*, Matrix metalloproteinase-9; *TIMP-1*, Tissue inhibitor of metalloproteinase 1; *LTB4*, Leukotriene B4; *TNF-α*, Tumour necrosis factor-alpha; *VEGF*, Vascular endothelial growth factor; *oxLDL*, oxidised low-density lipoprotein; *MLE*, mouth level exposure; *NFDPM*, nicotine free dry particulate matter; *QoL*, Quality of life; *FEV*, Forced expiratory volume; *FEV1*, Forced expiratory volume in 1 second; *PEF*, Peak expiratory flow; *4-ABP*, 4-aminobiphenyl.

## Methods/design

### Study design

This study will be a single-centre, single-blind, controlled clinical trial with a forced-switching design that will be conducted in Hamburg, Germany. The study will be partly clinic-based (residential) and partly ambulatory (non-residential, including brief visits to the clinic). This study will be conducted in compliance with the ethical principles of the Declaration of Helsinki, Good Clinical Practice [17,18] and German law. When the Principal Investigator signs the protocol, he or she will be agreeing to adhere to the instructions and procedures described in it.

The Principal Investigator or designated investigators will ensure that participants are given full and adequate oral and written information in non-technical terms about the nature, purpose, potential risks and possible benefits of study participation. Participants will be given time to consider all the information, the opportunity to ask questions and will be required to read, sign and date informed consent forms that summarise the discussion before participating in any procedures related to the study.

The protocol and the informed consent forms have been approved by the ethics committee of the Ärztekammer Hamburg, Hamburg, Germany (Processing Number PV3824).

The study has a forced-switching design to enable data to be obtained about changes in exposure to tobacco smoke toxicants and related biological effects. The effects of RTP cigarettes will thus be evaluated within individuals (switching smokers serve as their own control) and between individuals (switching versus non-switching smokers). The ex-smoker and never-smoker control groups will provide background levels of BoE arising from environmental sources. They will also provide reference levels of BoBE that would be expected in people who have given up smoking for at least 5 years or who have never smoked. The inclusion of multiple types of non-smoker control groups is anticipated to improve the interpretation of the data generated in this study.

Financial compensation for the inconvenience to and effort of participants will be offered as part of the study, but the sponsor does not wish this approach to incentivise participants to smoke. Stipends will, therefore, be calculated independently by the clinic according to the usual rates for this type of clinical study and will be approved by the ethics committee of the Ärztekammer Hamburg.

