**INDUCERS**			
**1A2**	**2B6**	**2C8**	**2C19**
N/A	Phenobarbital	N/A	N/A
	Phenytoin		
	Rifampin		
**2C9**	**2D6**	**2E1**	**3A4,5,7**
Rifampin	N/A	Isoniazid	Carbamazepine
Secobarbital			Phenobarbital
			Phenytoin
			Pioglitazone
			Rifabutin
			Rifampin
			St John’s wort
			Troglitazone

(Adapted with permission from Version 5.0 (http://medicine.iupui.edu/clinpharm/ddis/table.aspx)).

1A2, 2B6 etc = CYP enzyme subtypes.

For the smoking groups an additional exclusion criterion at screening is planning to quit smoking in the next 12 months (although cessation counselling will be available to smoking participants during and at the end of the study). For the non-smoking groups, additional exclusion criteria are smoking at any time during the study and regular exposure to second-hand smoke (e.g., through living in a household or working with smokers).

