### Study groups

Participants will be assigned to study groups primarily on the basis of whether they are smokers, ex-smokers or never smokers. The demographics for each group will be matched as far as possible (accepting the constraints of the minimum age difference between smokers and non-smokers) i.e. participants’ sex and age will also be taken into account. The assignment of control cigarettes or RTP cigarettes will be kept within cohorts, i.e., all participants in a smoker subgroup will be switched to the same study product at the same time to meet the restrictions posed by the predetermined schedule for the conduct of the study. For practical reasons, including clinic capacity and sample collection, the smoker and non-smoker groups will be further split into two subgroups (Figure 1). Therefore, to ensure enough participants are recruited to all subgroups, that subject availability will be assured and groups will be well matched for age and gender, we have accepted that full randomisation is not possible. Smokers will be recruited and subgroups filled according to order of screening, age, gender and availability at the study start time. Non-smokers will be recruited on the basis of the same criteria in an attempt to match the control group well with the smoker-group demographics.

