#### Ambulatory visits

Participants in the smoking groups will visit the clinic on the first day of the first ambulatory period (Figure 1). Smoking subjects will be asked to confirm the ISO tar yield of their usual brand and smoking status of all subjects will be verified by a urine cotinine test. Participants will be given a diet sheet to which they will be asked to adhere during specified times in ambulatory periods (i.e. 48 h before each in-clinic evaluation). Participants will be supplied with cigarettes according to their assigned product (Table 3) and daily consumption rate, plus two packs, and asked to smoke only the supplied brand until their next visit. Smokers will be allowed to smoke *ad libitum*, rather than according to a pre-specified quantity or timetable.

Each participant will be trained how to use an electronic diary in which he or she will be asked to document cigarette consumption, diet, exercise, medications and any other health-related issues on every ambulatory day. Participants will be required to bring the diary to every clinic visit.

Further ambulatory clinic visits will be made on days 31, 62, 95, 124, 144 and 165 (Figure 1). During these visits, diary entries will be checked, any protocol violations (e.g. consumption of cigarettes that were not supplied by the sponsor, significant health-related events or intake of excluded medications) will be assessed and decisions made about further participation in the study. Urine samples will be taken and tested for cotinine. Cigarette butts will be collected for analysis and the numbers of butts will be compared with diary entries and recorded. Participants will be supplied with further study cigarettes (normal daily consumption x number of days, plus two packs) and reminded to smoke only those until their next visit. They will also receive fresh tins to collect cigarette butts. The clinic staff will record information on hard copy case report forms during visits and will later be transcribed into an electronic system.

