In previous smoking studies based at the Hamburg clinic, it has been an absolute requirement of the ethics committee that smoking cessation counselling is provided to smoking subjects during the study. Therefore, several optional smoking-cessation workshops will be held during the study, for groups of 20–25 participants and led by a psychologist experienced in smoking cessation. The format will be a mix of lectures (including presentations, demonstrations and case studies), self-assessment (tests and questionnaires) and team and small-group work. The main aims of workshops will be to improve the knowledge of the participants about smoking cessation options, help participants to make realistic self-assessments regarding smoking cessation, increase participants’ motivation to quit or reduce smoking and develop individual plans for quitting or reducing smoking. Each workshop will take 60–90 min. Additionally, the Smoke-Free Programme of the Munich Institut für Gesundheitsförderung will be offered to all smoking subjects who wish to participate. The approach involves three meetings of 180 min and two telephone consultations. Following a preparatory phase, a day to quit smoking will be decided for all attendees. Strategies to handle irritation and critical situations and for behaviour control will be provided and alternative behaviours developed. In the final phase, the emphasis will be on prevention of relapse. Participants will be reminded of the dangers of smoking before enrolment, will be free to voluntarily quit smoking and withdraw from the study at any time and may still access the smoking-cessation workshops.

Ex-smokers and never smokers will be assessed in three in-clinic evaluations, on days 1–3, 78–80 and 162–164 (Figure 1, Table 7). As for the smoking groups, they will arrive in the evening of the first day and will remain in the clinic until the evening of final day of each visit.

**Table 7 T7:** Schedule for in-clinic evaluations of ex-smoker and never-smoker groups

**Day and suggested times**	**Sampling**	**Procedure**

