### Statistical analysis

The sample size estimate is based on observed data for BoE and BoBE and calculations made with MINITAB software version 15 (two-sample *t*-test). Percentages of reductions in smoke toxicants in the RTP versus commercial products are assumed to translate into corresponding reductions in BoE concentrations. Sample size calculations were performed to achieve a power of 80% to detect a difference between control and test products at an alpha level of 0.05. On the basis of the least sensitive BoE (aromatic amines), a sample size of 50 was determined to be adequate for all BoE of interest in this study (from study ISRCTN 72157335).

Similar estimates for BoBE are based on data for biomarkers in urine and plasma previously obtained by the sponsor and the least sensitive biomarkers in the literature, which showed that sample size of 50 would be adequate for BoBE in the primary objective. Literature search for secondary BoBE responses were uninformative, so sample size was assumed to be the same as for the primary outcomes.

On the basis of these calculations and a 6-week study in groups of 50 smokers (ISRCTN 72157335), it was estimated for this study that 70 participants per smoking group will be required to allow for anticipated attrition rates of up to 16% and achieve completion by at least 50 participants in each group. Sixty participants will be recruited to each of the ex-smokers and never-smoker control groups, as attrition is expected to be lower in these groups.

Statistical analyses will be performed by Celerion. A detailed statistical analysis plan will be prepared before database closure and agreed by the sponsor and Celerion. Any changes in the planned statistical methods will be documented in the study report.

The primary and secondary objectives will be examined by computing group biomarker levels at baseline, midpoints and at the end of the study (Table 1). Data for the primary outcome might be transformed to ensure that any assumptions associated with particular statistical tests or models are obeyed. ANOVA will be performed to identify differences between groups. As cigarette consumption may change over time or as a result of the switch, an ANCOVA will also be performed, using cigarettes per day as a covariate. For the secondary outcomes, an exploratory analysis with a matrix-type approach, such as principle component analysis, may be used.

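### Conclusions about the RTP cigarette should rest on RTP versus control referenced to the pre-switch value; the article ranks no comparison and names no baseline biomarker value

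*Protocol article*

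**What the plan says.** **Effect measures.** The Study design section of the protocol article says that RTP effects "will thus be evaluated within individuals (switching smokers serve as their own control) and between individuals (switching versus non-switching smokers". Neither comparison is given priority.

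**Analysis.** Under Statistical analysis: "The primary and secondary objectives will be examined by computing group biomarker levels at baseline, midpoints and at the end of the study", and "ANOVA will be performed to identify differences between groups". An ANCOVA on cigarettes per day is added, because consumption may shift with time or through the switch itself. The section does not say whether the ANOVA response is a level or a change. It does not mention the pre-switch biomarker value as a covariate or reference. The sample size is based on control versus test product.

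**Objective.** Study hypothesis and objectives describes the primary aim as a descriptive look at biomarker changes in individuals, within groups and across groups.

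**Allocation.** Study groups states that "we have accepted that full randomisation is not possible". Each smoker subgroup receives one product as a whole. Subgroups are filled by screening order, age, sex and availability.

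**Other influences on smoking.** Smokers smoke freely, "rather than according to a pre-specified quantity or timetable" (Ambulatory visits). Under Exclusion criteria, "cessation counselling will be available to smoking participants during and at the end of the study". The In-clinic evaluations section describes optional workshops meant to "increase participants’ motivation to quit or reduce smoking and develop individual plans for quitting or reducing smoking", and a further programme in which "a day to quit smoking will be decided for all attendees".

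**The concern.** The two comparisons answer different questions. A switcher's own before-after change contains the product effect plus anything else that moved smoking or biology over about six months, including counselling and time on study. The protocol itself reports a time effect. In earlier studies more than 90% of smokers raised consumption on the last study day, typically by two to three cigarettes, and the plan tries to mitigate this with a seven-day supply. Such influences could exaggerate or mask an RTP effect.

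The control arm deals with whatever the arms share. But if the between-arm comparison is made on levels, in cohorts not formed by full randomisation, a standing difference between cohorts stays in the result. The named covariate does not repair this: cigarettes per day is measured after the switch and, as the plan says, may respond to it.

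At stake is whether a reported RTP effect, especially on the biomarkers of biological effect, is a product effect or partly drift or cohort difference.

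**Working it through.** **1. The plan's figure.** The plan states 50 evaluable smokers per group (read as per group), a two-sample t-test, 80% power and alpha 0.05. No effect size or SD is given, so 50 cannot be reproduced. Solved backwards, two-sided, the detectable difference is (1.960 + 0.842) × √(2/50) = 0.56 SD.

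**2. What each contrast estimates.** On the log scale, let τ be the product effect, δ a shift shared by both arms, b a stable difference between cohorts already present before the switch, u any extra shift in the RTP arm from unequal counselling uptake, and ρ the baseline-to-end correlation (equal variances assumed).

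| Contrast | Estimates |
|---|---|
| Within-switcher change | τ + δ + u |
| RTP minus control, end levels | τ + u + b |
| RTP minus control, change from baseline | τ + u |
| RTP versus control, baseline-adjusted | τ + u + (1 − ρ)b |

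Every controlled contrast removes δ, the end-level one included. Only the baseline reference deals with b. None removes u.

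**3. Precision.** With n = 50 per arm, the detectable difference is 0.5603 SD × a factor: 1 for end levels, √(2(1 − ρ)) for change, √(1 − ρ²) for baseline-adjusted ANCOVA. The document gives no ρ, so a range is shown.

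| ρ | End level | Change | Baseline-adjusted |
|---|---|---|---|
| 0.3 | 0.560 | 0.663 | 0.535 |
| 0.5 | 0.560 | 0.560 | 0.485 |
| 0.7 | 0.560 | 0.434 | 0.400 |
| 0.9 | 0.560 | 0.251 | 0.244 |

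Change scores lose precision against end levels below ρ = 0.5. Baseline adjustment does not.

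**4. Illustration on assumed inputs.** None of these inputs is in the document: no product effect, CV 40%, ρ = 0.8, counselling attenders cut smoking by 20%.

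- SD(log) = √ln(1 + 0.4²) = 0.385.
- SE of within-arm change = 0.385 × √0.4 / √50 = 0.0345.
- SE of end-level difference = 0.385 × √(2/50) = 0.0771.
- SE of difference in change = 0.385 × √0.4 × √(2/50) = 0.0487. This is 1.41 times the within-arm SE and 0.63 times the end-level SE.
- Uptake of 25% in both arms: within-switcher change is 0.8^0.25 − 1 = −5.4%; both controlled contrasts centre on zero. In 10,000 simulated trials, a paired test at 0.05 flags 31%, end levels 4.6% and difference in change 4.8%.
- RTP cohort standing 10% lower as well: the end-level difference is −10.0% (26% flagged) and the difference in change 0.0% (5%). The baseline-adjusted difference is 0.2 × ln 0.9 = −0.021, about −2.1% (7%).
- Unequal uptake, 25% versus 15%: the difference in change keeps 1 − 0.8^0.10 = 2.2%. At 35% versus 15% it keeps 1 − 0.8^0.20 = 4.4%.

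**The case against.** The strongest reply is that this is detail for the statistical analysis plan, which the article says will be written before database closure. The objectives already speak of changes across groups. The analysis section collects levels at baseline, midpoints and end, which is all that a change needs. The trial is sized on control versus test, no within-arm test is specified, and the objective is called descriptive. Control smokers also see a cosmetic product change.

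Other features limit the bias. Counselling is optional, and smokers planning to quit are excluded. Groups are matched on age and sex as far as possible, and both arms smoke the same cigarette on days 1–14. Mouth-level exposure and puffing data help to separate behaviour from product. The article cites toxicant yield reductions of 10% to 95%, beside which a drift of a few percent would seldom change how most exposure biomarkers are read.

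Much of this stands. A reader might infer that the plan compares end levels only, or that counselling biases the RTP-versus-control comparison. The document supports neither: the ANOVA response is unspecified, and counselling effects common to both arms cancel in any controlled comparison.

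What remains does not depend on missing detail. The article positively presents own-control change as a measure of the RTP effect. The methods it does name make no use of the pre-switch biomarker value that the trial collects, in cohorts it says are not fully randomised.

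**Conclusion.** The point holds as a matter of stating the effect measure, not as a design error. The control arm and the baseline samples are in place. What is not stated is that conclusions rest on the controlled comparison and that it is referenced to the pre-switch value.

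The size cannot be taken from the document. The algebra in step 2 holds generally under its assumptions: within-switcher change carries all shared drift, end levels carry all of a stable cohort difference, and a baseline-adjusted comparison keeps about 1 − ρ of it.

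It is tempting to read the 31% or 26% as this plan's false-positive rates. They are not. They rest on an assumed CV, correlation, uptake and imbalance, and the 31% belongs to a paired test that the plan does not specify. Choosing between change score and baseline-adjusted ANCOVA in non-randomised cohorts is a judgement; either improves on leaving the baseline unnamed.

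**What to change.** In Study design and Statistical analysis, state that conclusions about the RTP effect rest on RTP versus control, referenced to the pre-switch in-clinic value (days 13–14). Use either the difference in change or an ANCOVA on the baseline biomarker value. Prespecify one as main and the other as a sensitivity check. Report within-switcher change as a description of total change from product, counselling and time. Treat the cigarettes-per-day ANCOVA as supportive.

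Leave the counselling offer as it is, since the ethics committee has required it in earlier studies at this clinic. Tabulate attendance and quitting by arm, because unequal uptake would leave residual bias under either method.

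The cost is wording and one small table, with no new samples. The change-score version needs no added participants if the baseline-to-end correlation is at least 0.5. Below that it is less precise than end levels (0.663 against 0.560 SD detectable at a correlation of 0.3), while baseline-adjusted ANCOVA is not. ANCOVA in turn keeps part of a standing imbalance, which is why the other method should be shown beside it.
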